### Sample — exclusion criteria

Patients with concomitant injuries with an intrinsic indication for surgery that led to a change in the rehabilitation protocol and patients with prior operations or injuries to the knee joint (both to the injured leg and to the contralateral leg) in the last 5 years are excluded.

Comorbidities that represent a contraindication for an active training programme (e.g. severe cardiovascular diseases, neurological diseases …) as well as underlying rheumatic diseases and pregnancy are also exclusion criteria.

### Recruitment

Participants are recruited at Sana Medical Centre in Cologne. During anamnesis (systematic interviewing of patients and collection of health data), the treating physicians apply the inclusion and exclusion criteria to screen and subsequently recruit the patients for participation if they give their voluntary informed consent.

The voluntary informed consent form must be personally signed and dated by the participants. The participants receive written information about the study, about possible effects on the functionality of the knee joint (e.g. improvement of mobility and strength) and possible risks (e.g. aching muscles after training) associated with study participation. There is no anticipated harm and compensation for trial participation.

Study participants can withdraw their consent for study participation at any time without giving reasons and without affecting subsequent treatment.

### Study procedure

After ACL injury, anamnesis/testing at the hospital and randomised allocation, participants perform the prehabilitation programme (intervention group: guided prehabilitation programme, comparator group: self-administered home training) (Fig. 3). The training starts at the earliest possible date and lasts until reconstruction (duration at least 3 weeks). For organisational reasons (scheduling of appointments at the hospital) as well as for medical reasons (increased risk of arthrofibrosis during surgery in the inflammatory phase), the period between injury and surgery is at least 3 weeks for most patients at the hospital. The length of the period between injury and surgery as well as all medical decisions (timing of surgery, graft used, etc.) are made independently of the planned study.

**Fig. 3 Fig3:**
[figure not shown]
Study flow chart: study procedure (enrollment, allocation, pre-surgery follow-up, post-surgery follow-ups) (ACL = anterior cruciate ligament)

Prior to surgical reconstruction (1–7 days before surgical reconstruction), the participants of both groups perform tests to assess the functionality of the knee joint guided by a therapist and complete selected questionnaires. Selected functional tests directed by a physician in the hospital and a questionnaire survey are also performed on the day of surgical reconstruction (postoperatively). There will be no special criteria for discontinuing or modifying allocated interventions. Patients will not be excluded from the study based on intention to treat. However, non-compliance will be monitored and reported.

While the prehabilitation programmes differ before surgery (guided training vs. home training), all participants participate in a standardised rehabilitation programme at PhysioSport after surgical reconstruction (Fig. 3).

### Organisation

Employees of the German Sport University (trial steering, monitoring and organisational support), Sana Medical Centre Cologne (recruitment of patients) and PhysioSport PACE GmbH (implementation of testing and training) are involved in the coordination. Those responsible are in close contact to each other. In addition, there is a meeting every month.

## Outcomes

Functional parameters as well as self-reported knee function will be collected in both groups at seven defined measurement time points (anamnesis in the hospital, 1–7 days before ACL reconstruction, on the day of surgery, and 30, 60, 90, and 180 days postoperative) (Fig. 4). The primary time point is 1–7 days before ACL reconstruction.

**Fig. 4 Fig4:**
[figure not shown]
Participant timeline and testing-tools (CRF = case report file, OP = operation, ROM = range of motion, KOOS Score = Knee Injury and Osteoarthritis Outcome Score, ACL-RSI = anterior cruciate ligament—Return to Sport Injury Scale)

### Primary outcome: self-reported knee function

The primary outcome of the study is the participants' self-perceived knee function, which is measured by the Knee Injury and Osteoarthritis Outcome Score (KOOS). The KOOS score is a measurement tool to assess participants' self-perceived knee function, especially after knee injuries such as ACL injuries [15, 19].

The KOOS score consists of 42 items in five subscales: pain, symptoms, function in daily living (ADL), function in sport and recreation (Sport/Rec) and knee-related quality of life (QOL). The mean of the subscale scores can be calculated and used to make an overall assessment of knee function [20]. The KOOS score has a high test–retest reliability. Overall, the minimum detectable change in patients with knee injuries is reported as 8–10 [16].

Since the KOOS score is used as the primary outcome in numerous randomised-controlled trials, there is a corresponding comparability of the results with other studies [19, 21]. Reference values of the KOOS score of patients after ACL reconstruction, of healthy subjects and active soccer players are also available and can be used for comparisons [22–25].

### Secondary outcomes

#### Functional outcomes

##### Range of motion

The active mobility of the knee joint (max. extension and flexion) is measured with a goniometer according to the neutral-zero method both preoperatively (following the anamnesis and 1–7 days before surgery) and postoperatively (on the day of surgery, 30 days and 60 days postoperative). The mobility of the knee joint is represented in a three-part code indicating the max. extension, the zero position as well as the max. flexion (e.g. 5°/0°/110°).

##### Neuromuscular control/activation

During the anamnesis, 1–7 days before the surgical reconstruction, on the day of the surgical reconstruction and 30 days after the surgical reconstruction, the participants are asked to perform an active extension of the leg while sitting (long sitting), i.e. to lift the extended leg from a mat (active stretch lifting = active lifting of the extended leg). The physician or therapist performing the test evaluates the performance as “not possible”, “possible with help” or “possible alone”.

##### Strength/torque (knee flexors and extensors, plantar flexors)

The strength of the knee flexors (hamstrings) and the knee extensors (m. quadriceps) is recorded 90 and 180 days postoperative using a strength test on the isokinet in a range of motion of 0°–90° (ROM 0°/0°/90°). For this purpose, maximum strength capacity is tested with 5 repetitions at 60°/s and strength endurance with 15 repetitions at 180°/s.

The strength of the plantar flexors (m. gastrocnemius) is tested with the “heel lift”. The participants stand upright with their legs extended and lift their heels off the floor to the maximum. Then one foot is lifted off the ground (single-leg stand) and the participants lift the heel off the ground maximally (plantar flexion). This test is performed both preoperatively (1–7 days before surgery) and postoperatively (after 60, 90 and 180 days). After 20 repetitions in full range of motion, the test is terminated. The therapist notes the number of repetitions the participant has completed in a side-by-side comparison (right/left) if the required number of 20 repetitions has not been reached.

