### Sample — inclusion criteria

Persons aged 16–60 years with unilateral and total primary ACL rupture (confirmed by magnetic resonance imaging) with indication for an arthroscopically assisted, anatomic ACL reconstruction using a hamstring or quadriceps tendon autograft who will be operated at Sana Medical Centre Cologne (inpatient or outpatient) are screened for inclusion. Participants can be included if the length of the period between injury and surgery is at least 3 and no longer than 13 weeks. Only participants who are able to give consent will be included. A parent or guardian must also sign the consent form for non-adult participants (16 or 17 years of age).

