### Sample size determination

The sample size calculation is based on the sum score of the KOOS (primary outcome parameter). The difference in the KOOS score of the comparator and intervention group at the measurement pre-reconstruction will be compared. The minimal clinically important change (MIC) for the KOOS score is reported to be a change of 8–10 with respect to the subscale score in patients with knee injuries [36]. For performing a sample size calculation, usually, a standard deviation of SD = 15 is used for the KOOS score [16]. On this basis, an effect size of *d* = 0.533 was calculated using G*Power [37]. With a power of 80% and a one-sided alpha error level of 2.5%, data must be collected from *n* = 114 participants (equal number of participants in comparator and intervention group of *n* = 57 participants).

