### Randomisation procedure

Participants will be randomly assigned to intervention or comparator group with a 1:1 allocation as per a computer-generated randomisation schedule using permuted blocks of random sizes. The block sizes will not be disclosed, to ensure concealment. All patients who give consent for participation and who fulfil the inclusion criteria will be randomised. Allocation concealment will be ensured, as the physician at the hospital will see the randomisation code not until the patient has been recruited into the trial. The physician will see the allocation after opening the opaque sealed envelopes.

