### Statistical analysis

The two-sided alpha-error threshold will be set at 5% for all inference statistical analyses: all p-values below this value will be considered as statistically significant. All statistical analyses will be performed using R statistic (R version 4.2.3 or newer). We will follow the CHAMP statement when designing and reporting the statistical analysis [38].

Baseline data will be displayed as means and standard deviations, while the main outcome data will be displayed as means and 95% confidence intervals.

Following plausibility control (physiological range check, formal outlier analysis), the main analyses will be conducted based on the intention-to-treat principle. For that purpose, a multiple imputation, assuming missing completely at random and using chained equations in a fully conditional specification with 40 iterations to produce asymptotically unbiased estimations of the data, will be performed.

The group affiliation of the participants (intervention group: prehabilitation, comparator group: home training) will be defined as a between-subject factor. The main analyses are calculated as linear mixed models for repeated measurements. Main inference statistical analyses will be performed using each outcome’s change scores from baseline to each follow-up as the dependent variable. These analyses will be performed confirmatory. The time effects (repeated measures) will be modelled as random effects (and factors), and the other independent variables (group) and covariates (potential confounders and effect modifiers) as fixed effects. In the same model, the influence on the treatment effect by clinically important confounders and effect modifiers age, gender, and activity level will be calculated.

Patients, who do not have surgery, will not be included. If patients will decide after inclusion that they do not want surgery after all, the last testing will be done before the originally scheduled surgery date (intention-to-treat).

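### The 90- and 180-day knee flexor and extensor strength models omit graft type, which leaves avoidable variance in these secondary endpoints

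*Protocol article*

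**What the plan says.** All places are in the protocol article.

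- **Sample — inclusion criteria:** patients need an indication for "anatomic ACL reconstruction using a hamstring or quadriceps tendon autograft". Two donor sites are therefore mixed in the trial.
- **Strength/torque:** "The strength of the knee flexors (hamstrings) and the knee extensors (m. quadriceps) is recorded 90 and 180 days postoperative". The isokinetic test covers the two possible donor muscle groups and has no preoperative measurement.
- **Study procedure:** "all medical decisions (timing of surgery, graft used, etc.) are made independently of the planned study". Graft type is neither fixed nor balanced by the design.
- **Randomisation procedure:** "1:1 allocation as per a computer-generated randomisation schedule using permuted blocks of random sizes". No stratification factor is named.
- **Statistical analysis:** the main models are called confirmatory and are built "using each outcome’s change scores from baseline to each follow-up as the dependent variable". For adjustment, the influence of "clinically important confounders and effect modifiers age, gender, and activity level will be calculated". Graft type does not appear as a stratum, covariate or subgroup.

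**The concern.** A hamstring graft is taken from the knee flexors and a quadriceps tendon graft from the knee extensors. If harvest weakens the donor muscle for some months, part of the spread in each strength result at 90 and 180 days reflects which graft a patient received. The direction would be opposite for flexors and extensors. None of the three named covariates records the donor site, and no baseline isokinetic value exists to take up differences between patients.

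Precision is what is at stake. Graft variation stays in the residual, confidence intervals for the two strength comparisons are wider than they need be, and some power is lost. Because the article lists its covariates and calls the models confirmatory, adding graft type after the data are seen would look post hoc. It has to be specified beforehand.

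**Working it through.** **1. The plan's own figure.** Sample size determination uses a KOOS difference of 8 with SD 15, so d = 8/15 = 0.533, with one-sided alpha 2.5% and power 80%. The noncentral t calculation gives power 0.799 at 56 per arm and 0.806 at 57, so 57 per arm (114 in total) is reproduced. The normal approximation gives 56 per arm, and power 0.813 at 57. Two-sided 5% requires the same number. This figure concerns KOOS before surgery, which graft harvest cannot affect. No power is stated for strength; below, 0.533 SD is borrowed only as a yardstick.

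**2. Inputs for strength.** From the document: 57 per arm, 1:1. Assumed, because the documents are silent: *p*, the share of patients with one of the two grafts, 0.1 to 0.5; and *g*, the difference in mean strength between grafts in within-graft SDs, 0.3 to 1.0. No dropout is allowed for.

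**3. Variance left in.** With the within-graft variance set to 1, the unadjusted variance is

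v = 1 + p(1 − p)g².

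The sample size needed for equal precision rises by the factor v and the SD by √v. By normal approximation,

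power = Φ(0.533 / √(2v/57) − 1.96).

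| p | g | v | √v | Power unadjusted | Power adjusted |
|---|---|---|---|---|---|
| 0.1 | 0.3 | 1.008 | 1.004 | 0.809 | 0.813 |
| 0.1 | 1.0 | 1.090 | 1.044 | 0.779 | 0.813 |
| 0.3 | 0.5 | 1.052 | 1.026 | 0.793 | 0.813 |
| 0.5 | 0.3 | 1.022 | 1.011 | 0.804 | 0.813 |
| 0.5 | 0.5 | 1.062 | 1.031 | 0.789 | 0.813 |
| 0.5 | 1.0 | 1.250 | 1.118 | 0.721 | 0.813 |

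The cost runs from 0.8% to 25% of the sample size, and the power loss from under half a point to about 9 points.

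**4. Chance imbalance is the same cost, not a second one.** The SD of the between-arm difference in graft share is √(2p(1 − p)/57): 0.056 at p = 0.1 and 0.094 at p = 0.5. The 95% range is therefore ±11 to ±18 percentage points, which moves the arm difference by ±0.03 to ±0.18 SD. But the variance of the unadjusted arm difference is

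(2/57)·v = 2/57 + g²·2p(1 − p)/57,

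and the last term is exactly the variance of that shift. The unadjusted standard error already contains it. At p = 0.5 and g = 1.0, √(2 × 1.25/57) = 0.209, against √(2/57) = 0.187 with adjustment.

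**The case against.** **Nothing stated is wrong, and the covariates could be left to the analysis plan.** An article may leave outcome-specific covariates to a fuller document, and an unseen analysis plan could include graft type. This limits the weight of the point. It does not remove it, because the article names its covariates for models it calls confirmatory and graft type is not among them.

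**Imbalance as bias.** A reader might infer that a chance difference in graft mix would be mistaken for a prehabilitation effect, so that the strength results are biased. The documents do not support this. Allocation is randomised 1:1 and graft choice is stated to be independent of the study. The unadjusted estimate is then unbiased on average, its type I error is valid, and its standard error already carries the imbalance.

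**Adjustment as risk-free.** A reader might also infer that graft type from the operation record can be adjusted for without removing any treatment effect. That goes too far. Surgery follows at least three weeks of training, only patients are blinded, and the hospital physician opens the allocation envelope. The independence statement does not say that graft is settled before randomisation, so the graft actually used may be a post-randomisation variable. This part of the objection stands and shapes the fix.

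**The size may be trivial.** This also stands. A 50:50 mix is the most favourable case for adjustment. If one graft dominates, or the donor effect is small, little is gained. The documents do not state that harvest weakens the donor muscle at these visits.

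**Conclusion.** The point holds as a modest loss of precision in secondary endpoints. Flexor and extensor strength are compared across two donor sites, with graft type in neither the randomisation nor the named covariates. Under the assumed ranges, the avoidable cost is about 1% to 25% of the sample size, with unadjusted power between about 0.81 and 0.72 for a 0.533 SD effect. Both the existence of a donor-muscle effect and its size are assumptions, as is the graft mix.

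The primary KOOS comparison, its sample size and the main conclusion are unaffected. This is a worthwhile refinement rather than a flaw that threatens the trial.

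**What to change.** 1. At t1, record the planned graft type on the enrolment form before the allocation envelope is opened.
2. In Statistical analysis, add planned graft type (hamstring or quadriceps tendon) as a fixed-effect covariate in the models for 90- and 180-day knee flexor and extensor strength.
3. State that these two outcomes are modelled as follow-up values. The change-from-baseline rule cannot apply to them, because isokinetic strength is not measured before surgery.
4. Report the graft actually used by arm, as a check on the stated independence of graft choice from the study.
5. Leave graft type out of the primary model, whose time point precedes surgery.

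Recording the plan before allocation makes the covariate a true baseline variable. It also gives a value for patients who are never operated on and would otherwise have none under the intention-to-treat imputation.

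The cost is one form item, a few lines of analysis text and one degree of freedom in secondary models. The gain is small if one graft dominates, and smaller still where the planned and actual grafts differ. Patients enrolled before the change may lack a pre-allocation record; the analysis text should say how they are handled.

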##### Dynamic postural control

The dynamic postural control is measured by the Y-balance test. The Y-balance test is a functional and unilateral dynamic balance test in a single-leg stance and is performed by participants 1–7 days before surgery and 60, 90 and 180 days postoperative. It checks the range of motion of the playing leg in the three directions anterior, posteromedial and posterolateral (mobility of the joints: knee joints, hip joints, ankle joints) [26], the strength of the lower extremity [27], the proprioception [27], the dynamic balance [28] and the neuromuscular control, postural control, postural stability, as well as the trunk stability [27, 29]. The best values from both sides (left/right) and each direction (anterior/posteromedial/posterolateral) are selected from the valid trials and a total score is calculated. If the total score for one of the legs or for both legs is lower than 94%, there is an increased risk of injury [29]. The total scores (left/right) are used for further calculation of the LSI. The LSI (limb symmetry index) is used to determine whether a deficient lateral deviation is present [30].

##### Jumping ability

Counter Movement Jump is used to assess jumping abilities in a slow lengthening-shortening cycle. It is performed at 90 and 180 days postoperative and tests the explosive power, the maximum strength and the vertical bounce [31]. With the aid of a force plate, the flight time and the impulse during the jump are determined so that the jump height can be calculated. In addition, the force development is recorded in relation to the body weight as well as the percentage difference of the maximum force development in the bilateral comparison of the legs (affected vs. unaffected leg).

##### Workability

In order to record the workability, the number of days absent from work is determined preoperatively and postoperatively. In addition, it is determined when the participants state that they are fully able to work again.

#### Return to sport

##### Psychological readiness

The ACL-Return to Sport Injury Scale (ACL-RSI) is used to assess self-confidence, risk assessment, and emotions related to the ACL injury as well as complaints and problems caused by the knee joint injury. Participants answer a total of 12 questions on the 10-point scale from 0 to 100 1–7 days before surgery and 30, 60, 90, and 180 days postoperative [32]. A total score is determined from the results of the 12 questions answered (score achieved/number of questions). If the total score is below 51%, this indicates a lack of confidence in the knee joint. The decision to return to sport after an ACL injury is significantly related to response on the ACL-RSI scale [32].

##### Return to sport — success

The RTS success is characterised by achieving the pre-injury level of sports participation as defined by the same type, frequency, intensity, and quality of performance as before the injury.

The participant’s activity level is assessed at an initial presentation at the hospital (anamnesis), 1–7 days prior to surgery and 30, 60, 90 and 180 days postoperatively using the Tegner score (11-point scale). The Tegner score was developed specifically to assess the activity level of participants with ACL injuries and rates it on a scale from 1 (low activity level) to 10 (professional level) [33–35].

### Sample size determination

The sample size calculation is based on the sum score of the KOOS (primary outcome parameter). The difference in the KOOS score of the comparator and intervention group at the measurement pre-reconstruction will be compared. The minimal clinically important change (MIC) for the KOOS score is reported to be a change of 8–10 with respect to the subscale score in patients with knee injuries [36]. For performing a sample size calculation, usually, a standard deviation of SD = 15 is used for the KOOS score [16]. On this basis, an effect size of *d* = 0.533 was calculated using G*Power [37]. With a power of 80% and a one-sided alpha error level of 2.5%, data must be collected from *n* = 114 participants (equal number of participants in comparator and intervention group of *n* = 57 participants).

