## Methods

### Aims

The planned study focusses on optimal content (criteria-based programme), general setting of preoperative training and supervision (one-on-one guidance or self-administered training). With this randomised-controlled trial, our objective is to compare the effects of a guided, structured and criteria-based preoperative rehabilitation programme, which can be adapted to the individual performance level, to a non-guided and self-administered home-based training programme on functional and self-report outcomes and secondary issues (other knee function, daily living and return to sport). The KOOS sum score (Knee Injury and Osteoarthritis Outcome Score) is the primary outcome and assesses the self-perceived knee function [15, 16]. We hypothesise that the guided prehabilitation programme will be more effective than self-administered home training relating to its effect on the baseline to pre-reconstruction change score of the KOOS sum score.

We will investigate the effects of pre-operative training (guided vs. unguided) at different time points (pre-op, 30/60/90/180 days post-op). We expect that the guided prehabilitation programme will have a particularly positive short-term effect and that the difference between the two groups will decrease over the progress of rehabilitation.

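### The sample size is worked out for the pre-operative KOOS score, but the planned test is on change from baseline without baseline KOOS as a covariate, so the 80% power is not shown for that test

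*Protocol article*

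**What the plan says.** Two sections of the protocol article describe two different primary quantities.

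- **Sample size determination** compares the arms on the score at the pre-operative visit (t2): "The difference in the KOOS score of the comparator and intervention group at the measurement pre-reconstruction will be compared". Its spread is that of a score: "usually, a standard deviation of SD = 15 is used for the KOOS score". With d = 0.533, and "With a power of 80% and a one-sided alpha error level of 2.5"%, it arrives at 57 per group, 114 in total.
- **Aims** puts the hypothesis on change, "relating to its effect on the baseline to pre-reconstruction change score of the KOOS sum score". **Statistical analysis** does the same for every outcome, using "change scores from baseline to each follow-up as the dependent variable", and calls these analyses confirmatory.

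The covariates named in Statistical analysis are age, gender and activity level. Baseline KOOS is not among them, although the Outcomes section has self-reported knee function collected at all seven time points, including t1.

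**The concern.** A score and a change score have different variances. If the SD is the same at both visits, the change score varies more than the score whenever the correlation between visits is below 0.5. A sample size that is right for one may then be too small, or more than enough, for the other. The document gives neither the SD of change nor the correlation, so a reader cannot tell which applies.

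At stake are power and precision. With no covariate for baseline KOOS, the change-score analysis subtracts the whole baseline value whether or not baseline predicts t2 that strongly. It therefore over-corrects chance baseline imbalance when the correlation is modest. The repeated-measures model does not cure this, because every change score for a patient subtracts the same t1 value.

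**Working it through.** **Inputs.** From Sample size determination: d = 0.533, SD = 15, hence a difference of 0.533 × 15 = 8, the lower end of the quoted 8–10; n = 57 per arm; one-sided 2.5%. From Statistical analysis: two-sided 5%, which gives the same critical value. Assumed, because the document is silent: the same SD of 15 at t1 and t2, a range of correlations rho, complete t2 data, and no variance explained by age, gender or activity level.

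**Step 1: reproduce the plan's figure.** For a two-sample t-test the noncentrality is (8/15) × √(57/2) = 2.85 on 112 degrees of freedom, giving 80.6% power. With 56 per arm it is 79.9%, so 57 per arm is the smallest size that reaches 80%. The plan's 114 is correct for a comparison of t2 scores.

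**Step 2: the planned change score.** SD of change = 15 × √(2(1 − rho)). At rho = 0.3 this is 15 × √1.4 = 17.75.

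**Step 3: t2 KOOS adjusted for t1 KOOS.** Residual SD = 15 × √(1 − rho²), with one degree of freedom lost. At rho = 0.3 this is 15 × √0.91 = 14.31.

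Power with 57 per arm and difference 8:

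| rho | SD of change | Power, change score | Residual SD, adjusted | Power, adjusted |
|---|---|---|---|---|
| 0 | 21.21 | 51.4% | 15.00 | 80.6% |
| 0.3 | 17.75 | 66.5% | 14.31 | 84.1% |
| 0.4 | 16.43 | 73.1% | 13.75 | 86.9% |
| 0.5 | 15.00 | 80.6% | 12.99 | 90.3% |
| 0.6 | 13.42 | 88.4% | 12.00 | 94.2% |
| 0.7 | 11.62 | 95.4% | 10.71 | 97.7% |

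**Step 4: break-even.** Change-score power reaches 80% at rho of about 0.49. If the t2 SD stays at 15 and the t1 SD differs, the variance of change equals the variance of the t2 score at rho = SD(t1) / (2 × SD(t2)). That is about 0.4 if the t1 SD is 20% smaller and about 0.6 if it is 20% larger.

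**Step 5: total N for 80% power.** The change score needs 158 at rho 0.3, 136 at 0.4, 114 at 0.5 and 92 at 0.6. The adjusted analysis needs 114 at rho 0, 104 at 0.3 and 86 at 0.5, so never more than planned.

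**Step 6: sensitivity to the other covariates.** If age, gender and activity level explained 10% of the variance of change (an assumption), the change-score SD would shrink by √0.9. Power would then be about 71%, 78% and 85% at rho 0.3, 0.4 and 0.5.

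**The case against.** The strongest reply is that no loss of power has been demonstrated. Rho is not in the document, and above about 0.5 the change score has more power than planned. This stands. The variable interval from injury to surgery (3 to 13 weeks) makes a low correlation conceivable, but nothing in the document fixes its value.

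Second, 15 may have been meant as the SD of a change. If so, 114 already fits the planned test and only the wording needs repair. The plain reading is a score SD, but the possibility cannot be excluded, and the text should settle it.

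Third, the planned covariates may absorb some variance, so the shortfalls tabulated for low rho are at the upper end. This also stands. Step 6 shows that it softens the issue without removing it.

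A reader might go further and infer that the trial is underpowered, or that the change-score result would be biased. The document supports neither. The first depends on an unstated rho. The second is wrong, because randomisation keeps the comparison of change scores unbiased and the type I error intact.

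A reader might also see a conflict between one-sided 2.5% in the sample size and "The two-sided alpha-error threshold will be set at 5% for all inference statistical analyses". These are equivalent here and give the same N.

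Finally, the outcome is called a sum score in some places, while the primary outcome section describes a mean of subscales ("The mean of the subscale scores can be calculated and used to make an overall assessment of knee function"). That deserves one definition, but it is a separate, minor matter and carries no weight in the power argument. Only the difference is tied to subscales ("is reported to be a change of 8–10 with respect to the subscale score in patients with knee injuries"); the SD of 15 is not.

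**Conclusion.** The mismatch is clear from the text: the sample size is for a t2 score, the confirmatory test is on change, and nothing stated links the two. The claimed 80% power is therefore not shown for the planned analysis. Under equal SDs of 15, a difference of 8, complete data and no help from the other covariates, change-score power runs from 51.4% at rho 0 to 95.4% at rho 0.7 and breaks even near 0.49. A shortfall is possible, not proven.

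Adjusting for baseline KOOS removes the dependence on a favourable rho: under the same assumptions power is 80.6% or more throughout. This should be fixed because it is a free gain in precision; it does not make the trial invalid as planned.

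**What to change.** 1. Add t1 KOOS as a covariate in the primary analysis of t2 KOOS, alongside age, gender and baseline activity level. The hypothesis can still be phrased as change: once baseline is in a linear model, the estimated group effect is the same whether t2 or t2 minus t1 is the dependent variable.
2. Do the same for continuous secondary outcomes measured at t1. Do not extend one linear model to every t1 outcome. The active leg-lift rating has three categories, and the Tegner score appears to be the activity-level covariate itself.
3. Rewrite Sample size determination for that analysis, with residual SD 15 × √(1 − rho²) if 15 is a score SD. State whether 15 is the SD of a score or of a change, and give rho as an assumption.

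The cost is one degree of freedom and a dated, documented amendment before any unblinded analysis, since the trial is registered and recruitment started on 01/04/2023. No extra patients or measurements are needed, because the planned change score already requires t1 KOOS.
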